**Methods:**

The evaluation will use a controlled, segmented interrupted time series design, spanning 3 distinct phases: preimplementation (2015 to 2020), implementation (2020 to 2022), and postimplementation (2022 to 2024) phases. The outcomes will be (1) suicide mortality, (2) hospitalizations for suicide attempts, and (3) emergency room visits for suicide attempts. Datasets covering September 2015 to August 2024 will be provided by public health organizations in both jurisdictions, that is, the Institut national de la santé publique du Québec and Santé publique France. In Quebec, control sites will consist of the 14 other health regions with a population of at least 50,000, while in France, control sites will include the 18 metropolitan areas with a status comparable to that of Brest Métropole. The analysis will focus on age- and sex-adjusted monthly rates of the specified outcomes, with an emphasis on changes across the study phases to assess the putative effectiveness of the CQFD-I intervention. We hypothesize that each study outcome will decrease by 20% at implementation sites compared to control sites between the preimplementation and postimplementation phases.

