### Study Objective

Our objective is to assess whether implementing a multimodal suicide prevention program across 2 countries—encompassing a universal strategy (a web portal focused on depression and social isolation), selective strategies (training for primary care physicians on depression and training for mental health professionals on suicide risk assessment and management), and indicated strategies (standardized postcrisis outreach and outpatient monitoring practices)—leads to a reduction in outcomes associated with suicidal behavior, such as suicide mortality, hospitalization due to suicide attempts, and visits to emergency rooms (ERs) for suicide attempts, compared to control sites and over time. We hypothesize that after 2 years of the CQFD-I program’s implementation, there will be a 20% reduction in suicide mortality, hospitalizations due to suicide attempts, and ER visits for suicide attempts compared to control sites. This reduction will be observed when comparing the postimplementation phase (beginning in 2022) to the preimplementation phase (ending in 2020).

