### Outcomes and Data Sources

Primary outcomes, which include the suicide mortality rates, hospitalization rates for suicide attempts, and ER visit rates for suicide attempts, will be obtained monthly across 3 phases: preimplementation (September 2015 to August 2020), implementation (September 2020 to August 2022), and postimplementation (September 2022 to August 2024) phases. Data will be collected for both the implementation and control sites in both countries.

We will access Quebec data from the Integrated Chronic Disease Surveillance System database available at the Institut national de santé publique du Québec (INSPQ) [43]. In Quebec, suicide deaths are recorded in the Registre des évènements démographiques–Fichier des décès database and correspond to the *International Classification of Diseases, 10th Revision* (*ICD-10*) codes X60 to X84 and Y87.0 [35]. Data on hospitalizations for suicide attempts are recorded in the Maintenance et exploitation des données pour l’étude de la clientèle hospitalière system and correspond to *ICD-10* codes X60 to X84 and Y87.0. We will only consider hospitalization cases when acute care is the documented reason for admission [35]. ER visits for suicide attempts are recorded in the Banque de données communes des urgences, which includes suicide attempts as one of the options that may be selected as the visits’ main reason by the nursing staff during triage [35]. For rate calculations, we will use the regional population per calendar year from official data published by the Ministère de la Santé et des Services sociaux du Québec [32]. We will benefit from technical support through collaboration with the INSPQ to ensure access to the most appropriate data sources and validate our data extraction procedures.

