### Statistical Methods

We will use the software Stata (StataCorp LLC) to analyze data with a segmented time series model in 3 phases (preimplementation, implementation, and postimplementation phases) and 2 arms (intervention and control areas), conforming to the following equation [27]: Y_t_ = β_0_ + β_1_T_t_ + β_2_X_i_ + β_3_X_p_ + β_4_(T_t_ – t_i_)X_i_ + β_5_(T_t_ – t_p_)X_p_ + β_6_G + β_7_GT_t_ + β_8_GX_i_ + β_9_GX_p_ + β_10_G(T_t_ – t_i_)X_i_ + β_11_G(T_t_ – t_p_)X_p_ + ε_tG_. In this equation, T_t_ is the time elapsed since the beginning of the preimplementation period (September 1, 2015); X_i_ and X_p_ are dummy variables, respectively representing the implementation and postimplementation phases (X=1 during this phase and X=0 during other phases); t_i_ and t_p_ are the first time points of the implementation and postimplementation phases; G=1 for cases and G=0 for controls; and ε_tG_ represents random error that combines ε_t1_ for cases and ε_t0_ for controls.

For all 3 outcome variables (suicide mortality, hospitalizations for suicide attempts, and ER visits for suicide attempts), we will generate monthly rates for each of the cases and control areas throughout the study period (September 2015 to August 2024, n=120 months). For our main analyses, we will adjust monthly rates by age and sex using direct standardization based on yearly data, with the year 2019 serving as the reference population for each implementation site. We will fit the above model using ordinary least square regression, with β_0_ through β_5_ included as pooled values between control areas. We will test for autocorrelation up to 12 lags to account for potential seasonality in our monthly data and adjust the model as per the results. In case of seasonality effect, we will also attempt using Fourier terms or flexible spline functions to fit the data better [46]. In our main analysis for each implementation site, we will treat the implementation phase as a transition period [47] and isolate the program-specific effects: (1) change in rates between the preimplementation and the postimplementation phases (β_8_ + β_9_), and (2) change in trend between the preimplementation and the postimplementation phases (β_10_ + β_11_).

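### Neither planned program effect estimates the hypothesised 20% reduction between the preimplementation and postimplementation phases

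*Protocol article*

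**What the plan says.** The Abstract (Methods) states the hypothesis as a contrast between phases: "each study outcome will decrease by 20% at implementation sites compared to control sites between the preimplementation and postimplementation phases". Study Objective words it first as "We hypothesize that after 2 years of the CQFD-I program’s implementation, there will be a 20% reduction in suicide mortality" (and in the two attempt outcomes), then says how it will be judged: "This reduction will be observed when comparing the postimplementation phase (beginning in 2022) to the preimplementation phase (ending in 2020"). Outcomes and Data Sources dates the last phase: "postimplementation (September 2022 to August 2024) phases", which is 24 months.

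Statistical Methods fixes a 12-coefficient segmented model. The phase dummies are described as "respectively representing the implementation and postimplementation phases (X=1 during this phase and X=0 during other phases"), so they are not cumulative. The slope terms are (T_t − t_i)X_i and (T_t − t_p)X_p, where "t_i_ and t_p_ are the first time points of the implementation and postimplementation phases". The implementation phase is treated as a transition. The main analysis for each site is then to "isolate the program-specific effects: (1) change in rates between the preimplementation and the postimplementation phases", given as β8 + β9, and (2) the corresponding change in trend, given as β10 + β11. No other program effect is named for the main analysis.

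**The concern.** The hypothesis concerns a difference between two phases. In a segmented model with slopes centred at the start of each phase, a level coefficient is the departure from the extrapolated baseline trend in one month. It equals the phase-average change only if the slope does not change as well. The plan gives the level sum the label of a change in rates between phases, which it does not measure.

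The program works through a web portal, training and care pathways, and its effect could plausibly build up or wane over 24 months. If it does, the level term and the phase average separate. The published main results would then contain no estimate, and no confidence interval, that can be set against the 20% in the hypothesis.

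**Working it through.** **1. The plan's own figures.** The Statistical Power section quotes power for a 20% decrease of 33.1% (suicide), 85.7% (hospitalizations) and 80.4% (ER visits) in Outaouais. A one-sample comparison of a one-year rate with a fixed rate, at two-sided α = 0.05, reproduces these: Φ[(m0 − m1 − 1.96√m0)/√m1], with m0 = population × rate and m1 = 0.8 m0.
- Suicide: m0 = 397,007 × 15.5/100,000 = 61.5 and m1 = 49.2. This gives Φ[(12.3 − 15.4)/7.02] = 33.1%.
- Hospitalizations (53.4 per 100,000): 85.6%.
- ER visits (46.8 per 100,000): 80.4%.

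So the power statement, like the hypothesis, concerns an average rate. It does not concern β8 + β9 or β10 + β11.

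**2. What the coefficients mean under the printed coding.** In the post phase X_i = 0, so β8 and β10 drop out. The program effect in month T (case departure from its baseline trend, minus the control departure) is

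effect(T) = β9 + β11(T − t_p).

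- At September 2022, T = t_p and the effect is β9 alone.
- β8 is the same quantity at September 2020, the first implementation month. The planned β8 + β9 therefore adds one-month gaps from two different phases.
- The post-phase slope change is β11 alone, not β10 + β11.
- Over the 24 post months T − t_p runs from 0 to 23, with mean 11.5. The phase-average effect is therefore **β9 + 11.5β11**.

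**3. If cumulative coding was intended** (X_i stays at 1 in the post phase, which the printed sums suggest), effect(T) = β8 + β9 + β10(T − t_i) + β11(T − t_p). The first-month gap is β8 + β9 + 24β10. The mean of T − t_i is 24 + 11.5 = 35.5, so the phase average is **β8 + β9 + 35.5β10 + 11.5β11**.

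**4. Known effect profiles.** These use noise-free data, a base rate of 100, flat controls, and 60, 24 and 24 months taken from the stated dates. Results are under the printed coding.

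| Program effect | True post mean | β8 + β9 | β10 + β11 per month | β9 + 11.5β11 |
|---|---|---|---|---|
| None in implementation; post grows 0 to −40 | −20 | 0 | −40/23 = −1.74 | −20 |
| None in implementation; post fades −20 to 0 | −10 | −20 | 20/23 = +0.87 | −10 |
| Flat −20 in both phases | −20 | −40 | 0 | −20 |
| −20 in implementation, 0 afterwards | 0 | −20 | 0 | 0 |
| Ramp from 0 at −20/24 per month in implementation, then flat −20 | −20 | −20 | −0.83 | −20 |

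The first two rows hold for β8 + β9 only because the gap at the first implementation month is set to zero. They are unchanged under cumulative coding. Under that coding the last row gives β8 + β9 = 0, although the effect is a sustained −20, while the contrast in step 3 gives 35.5 × (−0.833) + 11.5 × 0.833 = −20.

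**The case against.** Level change and slope change are the usual outputs of a segmented model, and combining them is a post-estimation step that a condensed article may leave to its analysis plan. That would answer a complaint about missing detail. Here, however, the article names the main-analysis contrasts and gives one of them a description it does not fit.

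A reader might infer that a fading effect could confirm the hypothesis, or that a slowly building one would be missed. The document does not support this. It contains no rule that the level term alone decides, it names the trend change as a second effect, and the Statistical Power section says slope is assessed in addition to level. In the examples the trend term is +0.87 or −1.74 per month and would reveal the pattern, subject to its precision.

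A reader might also infer that the planned level term is the gap at the first post month. As printed it is not: β9 is that gap, and β8 + β9 equals it only when β8 is zero.

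A precision argument for the average would carry little weight. With independent errors its standard error is only about 6% smaller than that of the first-month gap.

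Finally, the phrase about two years of implementation could be read as a time point at the start of the post phase. The sentence that follows it, and the Abstract, state a phase comparison.

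**Conclusion.** The point stands in limited form. The hypothesis is a phase-to-phase reduction of 20%, and neither β8 + β9 nor β10 + β11 estimates it under either coding. The label attached to β8 + β9 is wrong as written. The discrepancy can be as large as the hypothesised effect: a level term of 0 when the phase mean is −20%, −20 when the mean is −10%, or −40 when the effect is a steady −20% from the start of implementation.

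These sizes rest on linear effect profiles, noise-free data and, for the growing and fading cases, no effect in the implementation phase. They show what the contrasts measure and do not predict the results. The phase average used here is measured against the model's own extrapolated baseline and the control changes. The coefficients are also on an absolute scale, so even the correct contrast needs converting before it can be compared with 20%.

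**What to change.** 1. State whether X_i and X_p are phase-only or cumulative, and make the equation and the contrasts agree.
2. For each outcome and site, prespecify the mean program effect over September 2022 to August 2024 with its confidence interval: β9 + 11.5β11 under the printed coding, or β8 + β9 + 35.5β10 + 11.5β11 under cumulative coding.
3. Report it also as a percentage of the model-based counterfactual rate for the same 24 months. Under the printed coding the mean counterfactual is β0 + β6 + (β1 + β7)T̄ + β3 + 11.5β5, where T̄ is the mean of T_t over those months. Give an interval for the ratio.
4. Report the first-month level change, the slope change and the month-24 effect as descriptive components, under labels that say what each one is.

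The cost is a decision on coding, one linear combination and one ratio from the same fitted model, and revised wording. No extra data are needed. Data collection is planned for September 2027, so the change can be fixed before the data are seen.

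### The main program-effect contrasts (β8+β9 and β10+β11) do not match the phase dummies as defined, so they add the implementation-phase change to the pre-to-post effect

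*Protocol article*

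**What the plan says.** All the relevant text is in the protocol article, Statistical Methods, apart from the dates and the hypothesis.

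- **Coding.** X_i marks the implementation phase and X_p the postimplementation phase, with "X=1 during this phase and X=0 during other phases".
- **Program terms in the model.** "β_8_GX_i_ + β_9_GX_p_ + β_10_G(T_t_ – t_i_)X_i_ + β_11_G(T_t_ – t_p_)X_p", where G is 1 for the implementation site and "t_i_ and t_p_ are the first time points of the implementation and postimplementation phases".
- **Main contrasts.** The program-specific effects are the "change in rates between the preimplementation and the postimplementation phases (β_8_ + β_9" and the "change in trend between the preimplementation and the postimplementation phases (β_10_ + β_11".
- **Role of the middle phase.** In that same main analysis, "we will treat the implementation phase as a transition period".

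Outcomes and Data Sources dates the phases as "preimplementation (September 2015 to August 2020), implementation (September 2020 to August 2022), and postimplementation (September 2022 to August 2024) phases". The hypothesis these contrasts must address, in Study Objective, is that "there will be a 20% reduction in suicide mortality, hospitalizations due to suicide attempts, and ER visits for suicide attempts compared to control sites", comparing postimplementation with preimplementation.

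**The concern.** The coding makes the two dummies mutually exclusive: when the postimplementation phase begins, X_i returns to 0. The terms carrying β8 and β10 are both multiplied by X_i, so neither contributes to a fitted postimplementation rate. A contrast meant to compare postimplementation with preimplementation therefore should not contain them, yet both stated contrasts do.

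These are the headline estimates for all three primary outcomes at both sites. An analyst who follows the text literally would report a quantity that is not the hypothesized pre-to-post change. It could overstate the effect, hide it, or show one where none exists, depending on what happened between September 2020 and August 2022. Adding that phase's coefficients also sits badly with treating it as a transition.

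**Working it through.** The plan states contrasts rather than a numerical result here, so the check is algebra on its equation, followed by noise-free fits with known answers.

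**Inputs.** The equation, the coding and the contrasts come from Statistical Methods. Phase lengths from the stated dates are 60 + 24 + 24 = 108 months. Counting September 2015 as month 0, t_i = 60 and t_p = 84. (The article's 120 months does not agree with its dates. That is a separate matter, and the dates are used here.)

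**Step 1: case minus control under the stated coding.**

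- Pre: β6 + β7·T
- Implementation: β6 + β7·T + β8 + β10·(T − t_i)
- Post: β6 + β7·T + β9 + β11·(T − t_p)

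Subtracting the extrapolated pre line from the post line leaves β9 + β11·(T − t_p). The level change at t_p is β9 and the trend change is β11. The stated sums equal these only if β8 = 0 (level) and β10 = 0 (trend).

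**Step 2: the same under cumulative coding (X_i stays 1 after t_i).** The post line becomes β6 + β7·T + β8 + β10·(T − t_i) + β9 + β11·(T − t_p). At T = t_p, T − t_i = 84 − 60 = 24, so the departure from the pre-trend is β8 + β9 + 24·β10. The trend change is β10 + β11. The stated trend sum is then correct. The stated level sum is correct only if β10 = 0.

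**Step 3: size.** The table shows deterministic case-minus-control paths, in percent of baseline, with controls flat. The effect sizes are assumptions chosen for illustration.

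| Path | True level change | β8+β9, stated coding | β8+β9, cumulative coding |
|---|---|---|---|
| -10% in implementation, -20% post | -20 | -10 + (-20) = -30 | -10 + (-10) = -20 |
| -15% in implementation only, 0 post | 0 | -15 + 0 = -15 | -15 + 15 = 0 |
| -20% in both phases | -20 | -20 + (-20) = -40 | -20 + 0 = -20 |
| +10% in implementation, -20% post | -20 | 10 + (-20) = -10 | 10 + (-30) = -20 |
| Linear ramp to -20% over implementation, then flat | -20 | 0 + (-20) = -20 | 0 + 0 = 0 |

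The true trend change is zero in every row. In the ramp row, β10 = -20/24 = -0.83 points per month. Under the stated coding β11 = 0, so β10+β11 reports -0.83 points per month. Under cumulative coding β11 = +0.83 and the sum is correctly 0, while the level needs 0 + 0 + 24·(-0.83) = -20.

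In rates, with the Outaouais suicide baseline of 15.5 per 100,000, a 20% change is 3.10. The first row would be reported as -4.65 instead of -3.10.

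**Step 4: precision.** With one case series, one pooled control series and independent errors of equal variance, the standard errors in units of the residual SD under the stated coding are:

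- Level: β9 0.823; β8+β9 1.250; ratio 1.250/0.823 = 1.52
- Trend: β11 0.0430; β10+β11 0.0626; ratio 0.0626/0.0430 = 1.46

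The corrected cumulative contrasts have the same standard errors as β9 and β11, as they should, because the two codings are reparametrizations of one model.

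**The case against.** The strongest reply is that the dummy definition may be the slip, not the contrasts. The sums are natural under cumulative coding, and the equation is taken from a cited source that is not shown. On that reading the trend contrast is exactly right, and the level contrast is right in every illustrative path without a slope during implementation. The text alone cannot show which sentence the authors meant, so the -30%, -15%, -40% and -10% figures apply only if the printed coding is used together with the printed sums. The paths are also invented, and the real error depends on the unknown β8 and β10. The standard-error ratios assume independent errors, whereas the plan will test for autocorrelation and adjust. The exploratory two-phase models would show a different picture.

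Most of this stands as a limit on the magnitudes, but it does not remove the contradiction. No other part of the article gives a different coding, and the printed one is explicit. Cumulative coding rescues only the trend sum in general. The level sum still fails if there is an implementation-phase slope. Such a slope is plausible, since the Results section says the five strategies were all fully in place only by September 1, 2022. The two-phase models are labelled exploratory and do not repair the main contrasts.

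**Conclusion.** The point holds. Under the coding the protocol states, both main contrasts are wrong: the pre-to-post program effects are β9 and β11. Under the alternative cumulative coding, the level contrast is still incomplete by 24·β10. On either reading at least one main contrast needs correcting for every outcome and site.

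The algebra needs no assumption beyond the printed equation and phase dates. The error in the level estimate equals β8 and the error in the trend estimate equals β10 under the stated coding, so its direction and size cannot be known in advance. The illustrations range from doubling a true 20% reduction to halving it, or creating an apparent 15% reduction from none. The precision loss (1.52 times for level, 1.46 times for trend) rests on independent, equal-variance errors.

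**What to change.** Amend the sentence that defines the contrasts, choosing one coding and keeping to it.

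- **Keep the stated coding.** Report β9 as the level change at September 2022 against the preimplementation trend, and β11 as the trend change.
- **Use cumulative coding.** Redefine X_i as 1 from t_i onward, and report β8 + β9 + 24·β10 (level) and β10 + β11 (trend).

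The two options give identical estimates and standard errors. Because the hypothesis concerns a whole phase rather than its first month, it would also help, though it is not needed to resolve the mismatch, to report the average effect over the 24 postimplementation months. Under the stated coding this is β9 + 11.5·β11, since the mean of months 0 to 23 is 11.5.

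The cost is one sentence in Statistical Methods, plus the dummy definition if the second option is chosen. No data or design element changes, and the Results section puts data collection and the start of analysis in September 2027, so the correction can be made before any result exists.

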The public health and social services of Outaouais have been under the jurisdiction of a single regional authority since 2015 [38]. This is also the case for most regions included in Tables 1 and 2, except for the following: Capitale-Nationale (n=2 distinct health authorities), Montréal (n=10), Côte-Nord (n=2), Gaspésie-Îles-de-la-Madeleine (n=2), and Montérégie (n=3). In the 2019 to 2020 financial year, 437 general practitioners billed universal health insurance of Quebec for services provided in Outaouais, with two-thirds using primary care–specific codes (Données de facturation RAMQ des médecins omnipraticiens, unpublished data, December 2023). This corresponds to 0.72 primary care physicians per 1000 residents (sixth rank). From 2016 to 2019, age-adjusted suicide rate of Outaouais averaged 15.5 per 100,000 overall (11th rank), 24.9 per 100,000 among male individuals (11th rank), and 6.4 per 100,000 among female individuals (seventh rank) (l’Infocentre de santé publique, unpublished data, November 2023). The average rate of hospitalizations for suicide attempts in Outaouais was 53.4 per 100,000 from 2016 to 2019 (eighth rank), and the average rate of ER visits for suicide attempts was 46.8 per 100,000 (10th rank) [35].

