For sensitivity analysis, we will replicate the calculations described in this section with various combinations of control areas pooled within the control group. These exploratory analyses will consider various cutoffs for each of the indicators presented in Tables 1 and 2 as potential criteria for control selection. In addition, we will use any information available at the time of data analysis to identify other suicide prevention programs or services that may have differentially impacted the implementation sites or specific control areas, and to justify testing other combinations of control groups. Furthermore, we will test alternative time series models, including 2 phases instead of 3, using bimonthly and trimonthly rather than monthly data, and stratifying by sex and age groups when allowed by power considerations. We will clearly report these analyses as exploratory to avoid distracting from the main study results.

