### Statistical Power

For the Outaouais region (n=397,007), the statistical power to detect a 20% decrease from the 2016 to 2019 averages at α=.05 would be 33.1% for suicide mortality, 85.7% for hospitalizations, and 80.4% for ER visits [48]. We do not yet have access to suicidal behavior data specifically for Brest Métropole; however, we estimated the statistical power based on its 2019 population (n=211,156) and published data about the Finistère department as a whole: the suicide rate was 23.4 per 100,000 in 2015 and the hospitalization rate was 227.8 per 100,000 in 2017 [45]. From this lower population but considerably higher rates of suicidal behaviors, the statistical power to detect a 20% decrease at α=.05 in Brest Métropole would be 26.8% for suicide mortality and 99.7% for hospitalizations. We did not find a reported rate of ER visits for suicide attempts in Finistère for the same period; however, cursory calculations indicate a base rate approximating 130 per 100,000 and a statistical power higher than 90%.

Given the low incidence of suicide in the general population, statistical power is often an issue when conducting pre-post rate comparisons. This has been reported as a justification to aggregate suicide mortality and suicide attempts in OSPI-Europe [12]. However, the statistical power benefits of variables aggregation would be marginal compared to including hospitalizations and ER visit rates as distinct primary outcomes, both of which can be assessed with satisfactory statistical power. Moreover, interrupted time series will provide additional benefits relating to the statistical power of this study in two important ways: (1) including a high number of repeated observations (n=120 months) [49] and (2) assessing the intervention effect on the outcome slope in addition to their level [50]. Considering the very different implications of death rates and indicators influenced by service use, we will analyze each primary outcome separately.

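### Every alternative model named keeps the straight-line site-minus-control slope, so agreement among them does not test it, and that slope costs the level effect much of its power

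*Protocol article*

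**What the plan says.** The model in the protocol article's Statistical Methods gives each implementation site its own baseline slope relative to controls (β7, the group-by-time term). It codes the three phases with mutually exclusive dummies. For the main analysis, "we will treat the implementation phase as a transition period". The reported effects are a level change and a trend change between the pre and post phases.

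The sensitivity paragraph refits the same calculations with other control pools, then adds: "we will test alternative time series models, including 2 phases instead of 3, using bimonthly and trimonthly rather than monthly data", plus sex and age strata. All are labelled exploratory. Fourier or spline terms are mentioned only for seasonality.

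Study Objective puts the hypothesis as a comparison of phases: "This reduction will be observed when comparing the postimplementation phase (beginning in 2022) to the preimplementation phase (ending in 2020".

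Statistical Power gives, "For the Outaouais region (n=397,007", a chance of success as follows: "the statistical power to detect a 20% decrease from the 2016 to 2019 averages at α=.05 would be 33.1% for suicide mortality", and "85.7% for hospitalizations, and 80.4% for ER visits". It then says the time series design adds to power, in part by "assessing the intervention effect on the outcome slope in addition to their level".

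**The concern.** The counterfactual for the post phase is the baseline site-minus-control line, carried forward over the two transition years. The post phase lies 25 to 48 months beyond the last baseline month. If the differential trend was not straight, or its estimate is noisy, the level effect inherits the error.

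A sensitivity analysis should vary the assumption that matters most. Here the named models vary the time unit, the control pool, the phase count and the stratum, and all keep β7. A set of agreeing results could be taken as support for a projection that none of them examined.

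The power text adds to the problem. It presents slope modelling as a gain on top of figures that were computed without any slope, whereas estimating a slope widens the standard error of the level effect.

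**Working it through.** **Inputs.** Outaouais population 397,007. Annual rates per 100,000: suicide 15.5 ("age-adjusted suicide rate of Outaouais averaged 15.5 per 100,000 overall"), hospitalization 53.4, ER visits 46.8 (Outaouais Region and Control Sites). Brest: population 211,156, with the Finistère rates 23.4 (suicide) and 227.8 (hospitalization) from Statistical Power. Phases of 60, 24 and 24 months (Outcomes and Data Sources). The article also states 120 months, but its dates give 108, which is used here.

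**1. The stated powers reproduce.** Take a one-sample, two-sided test of one year's site population against a fixed rate: power = Φ[(p0 − p1 − 1.96√(p0(1−p0)/n)) / √(p1(1−p1)/n)], with p1 = 0.8·p0. For Outaouais hospitalizations the expected counts are 212.0 and 169.6, so (42.4 − 28.5)/13.0 ≈ 1.07, giving 85.7%. The same formula gives 33.1% (suicide), 80.4% (ER visits), and 26.8% and 99.7% for Brest. It contains no control group and no slope.

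**2. Variance under the planned model.** Number the months 0 to 107. Baseline is 0–59 (mean 29.5, Sxx = 17,995) and post is 84–107 (mean 95.5, Sxx = 1,150). Let σ² be the monthly variance.

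- Level at month 84: 1/60 + 54.5²/17,995 + 1/24 + 11.5²/1,150 = 0.338σ². The baseline slope term is 0.165, or 49%.
- Post-phase average: 1/60 + 66²/17,995 + 1/24 = 0.300σ². The slope term is 0.242, or 81%.
- Trend change: 1/17,995 + 1/1,150 = 0.000925σ². The slope share is 6%.
- Phase-mean contrast, no slope: 1/60 + 1/24 = 0.058σ².

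The standard error of the level effect is √(0.338/0.058) = 2.4 times that of the phase-mean contrast. For the post-phase average the ratio is 2.3.

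**3. Power for a true 20% drop.** Set σ² to the monthly mean count (Outaouais hospitalizations: 397,007 × 53.4/100,000/12 = 17.7). Power = Φ(0.2·mean/SE − 1.96).

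| Outcome | Level, month 84 | Post-phase average | Phase means |
|---|---|---|---|
| Outaouais hospitalizations | 30% | 33% | 94% |
| Outaouais ER visits | 27% | 30% | 90% |
| Outaouais suicide | 12% | 13% | 47% |
| Brest hospitalizations | 59% | 64% | 99.9% |
| Brest suicide | 10% | 11% | 39% |

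Control noise is ignored. For Quebec it adds only 397,007/8,060,579 = 4.9% to the variance, and the first row becomes 29%, 32% and 93%.

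**4. Do the named alternatives test the projection?** Correlations with the main model's post-phase average, from the least-squares weights:

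- bimonthly 1.000; trimonthly 0.999;
- 2 phases, implementation dropped: 1.000;
- 2 phases, implementation merged into post (effect over the same months): 0.991;
- 2 phases, implementation merged into baseline: 0.61, with the projection reaching only 1 to 24 months;
- phase-mean contrast (not named): 0.44.

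As an illustration, assume no program effect and a differential baseline drift of +2% a year that stops at month 60. The main model's post-phase average is then biased by −2% × (95.5 − 60)/12 = −5.9 points. The first four alternatives give the same −5.9, and merging into baseline gives −3.7. The phase-mean contrast gives +2% × (60 − 29.5)/12 = +5.1, so it would reveal the dependence.

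**The case against.** The strongest reply is that this asks for one more model in an open list (the text says the alternatives are included, not exhaustive), in a condensed article whose analysis plan is not shown. That limits the weight of the point. It does not remove it, because the alternatives that are stated share one blind spot and the power rationale is wrong for the level effect.

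Several stronger readings are tempting and are not supported:

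- A reader might infer that a fragile result is bound to look robust. It is not. The 2-phase model is undefined, and if implementation joins the baseline it could well disagree with the main result. If implementation joins the post phase, the level coefficient moves to the first implementation month, which is a different quantity. The article also never says that agreement would prove robustness.
- A reader might take 81% as the slope's share of the reported effect. That share belongs to a post-phase average, which the article does not report. The level change has 49%, and for the trend change, at 6%, noise in the 24 post months dominates.
- A reader might think Study Objective prescribes a contrast without trends. It compares phases, but the same section asks for comparison over time, and Objectives says time will be considered.

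The no-slope contrast is precise only if trends are parallel. For Outaouais hospitalizations its standard error is 5.7% of baseline. A differential drift of 1% a year (bias 5.5 points over the 66 months between phase centres) would give about 16% false positives, and 2% a year about 48%. It cannot replace the main model.

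On power, the article is right that slopes allow a second effect to be assessed. What fails is the suggestion that this adds to power for the level effect.

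**Conclusion.** The point holds in this form. No named alternative drops β7, and the bimonthly and trimonthly refits cannot test the straight-line projection. The slope supplies about half the variance of the level change at month 84. Power for a 20% drop in Outaouais hospitalizations is about 30% to 33% with the slope, against about 94% for phase means and the stated 85.7%. The stated powers therefore do not apply to the planned model.

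The figures assume Poisson monthly noise, independent months, negligible control noise and, for Brest, the Finistère rates. Overdispersion or positive autocorrelation would lower all the powers. They also assume correctly coded contrasts: with exclusive dummies, β9 and β11 compare post with baseline. The sum β8 + β9 as written is noisier still (0.884σ standard error, about 15% power with control noise included).

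**What to change.** In the sensitivity paragraph of Statistical Methods, prespecify one secondary analysis per site and outcome beside the main model: the site-minus-control difference in mean monthly rate, post minus pre, with implementation months excluded and no group-by-time terms. Report it with β7 and its 95% CI. State that it is valid only under parallel trends and that a drift of 1% a year biases it by about 5.5 points.

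Read any disagreement in the light of β7's interval, without a pass/fail rule for robustness. Even under exactly parallel trends the no-slope estimate and the main model's post-phase average differ by chance with variance 0.242σ², about ±23 points (95%) for Outaouais hospitalizations, so such a rule would often reject sound results.

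Define the 2-phase model, and state that the re-binned refits do not test linearity. In Statistical Power, say that the trend terms allow a slope effect to be assessed but reduce precision for the level effect, and that the stated powers come from a one-year comparison with a fixed rate and do not apply to the planned model.

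The cost is a few sentences and one extra fit per site and outcome, with no new data. Data collection is planned for September 2027, so the change can be made before results are seen. The downside is the added analysis's reliance on parallel trends, which is why it should stay secondary.
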